## Abstract

Background: Cerebellar and motor tracts are frequently impaired in multiple sclerosis (MS). Altered hand dexterity constitutes a challenge in clinical practice, since medical treatment shows very limited benefits in this domain. Cerebellar control is made via several cerebellocortical pathways, of which the most studied one links the cerebellum to the contralateral motor cortex via the contralateral ventro-intermediate nucleus of the thalamus influencing the corticospinal outputs. Modulating the activity of the cerebellum or of the motor cortex could be of help. Method: The main interest here is to evaluate the efficacy of transcranial direct current stimulation (tDCS), a noninvasive brain stimulation technique, in treating altered dexterity in MS. Forty-eight patients will be recruited in a randomized, double-blind, sham-controlled, and crossover study. They will randomly undergo one of the three interventions: anodal tDCS over the primary motor area, cathodal tDCS over the cerebellum, or sham. Each block consists of five consecutive daily sessions with direct current (2 mA), lasting 20 min each. The primary outcome will be the improvement in manual dexterity according to the change in the time required to complete the nine-hole pegboard task. Secondary outcomes will include fatigue, pain, spasticity, and mood. Patients’ safety and satisfaction will be rated. Discussion: Due to its cost-effective, safe, and easy-to-use profile, motor or cerebellar tDCS may constitute a potential tool that might improve dexterity in MS patients and therefore ameliorate their quality of life.

## 1. Introduction

Multiple sclerosis (MS) is a chronic progressive inflammatory disease of the central nervous system and represents a major cause of non-traumatic disability in young adults [1,2]. Throughout the disease course, patients experience sensorimotor, emotional, cognitive, and behavioral symptoms. Among these symptoms, hand movements are frequently altered in MS; this results in a significant amount of disability [3,4,5].

Hand function is crucial for everyday life and its alteration, like in the context of MS, might constitute a real obstacle to living an independent life. In normal individuals, hand movements are perfectly balanced and coordinated allowing to execute functions with marvelous precision. “Dexterity” refers to the precise manipulation of objects and plays an important role in daily activities [6,7]. Performance of any activity requires complex sensory feedback from the external environment, sensorimotor integration, motor planning, execution, and adaptation. Such interaction plays an important role in adapting movement to environmental changes through rapid adjustments in motor control [8,9,10]. Data from neuroimaging studies have shown the contribution of many cerebral cortical areas (i.e., of motor cortex, cerebellum, and basal ganglia) in providing the optimal dexterity [11,12,13,14,15,16,17,18,19]. Motor cortex and basal ganglia generate voluntary and automatic movements, respectively. The cerebellum receives and integrates multisensory inputs (proprioceptive, visual, tactile, and vestibular), and adjusts the motor output accordingly [20]. Therefore, the cerebellum contributes to various aspects of motor control, such as postural stabilization, coordination, precision, and timing of movements. Cerebellar control is made via several pathways; the most studied one being the cerebellothalamocortical pathway. The latter links the cerebellum with the contralateral motor cortex via the contralateral ventro-intermediate nucleus of the thalamus and therefore could influence the corticospinal outputs [21,22,23]. The available literature supports the existence of a tonic facilitation of the motor activity exerted by the deep cerebellar nuclei, whereas putting the Purkinje cells in action would result in phasic inhibition of the mentioned nuclei and therefore “disfacilitation” of motor circuits [24].

In case of cerebellar dysfunction resulting from MS-related pathological changes, performing precise movement might be impossible. In fact, altered hand dexterity could affect 76% of MS patients, is associated with the deterioration of the overall upper limb activity and disuse, increases the need for more assistance and the perceived difficulties with activities of daily living [25,26,27]. Facing this source of disability, the available medical treatments showed very limited benefits in improving hand dexterity. Noninvasive brain stimulation (NIBS) techniques seem appealing tools to treat various neuropsychiatric complaints, including those encountered in patients with MS [28]. Transcranial direct current stimulation (tDCS) is a relatively new NIBS technique with a good safety profile, easy implementation, good patients’ tolerance, and little or no adverse effects [29,30,31,32,33,34,35]. It could modify spontaneous neuronal excitability and activity by tonic depolarization (anodal tDCS) or hyperpolarization (cathodal tDCS) of the neuronal resting membrane potential [36,37]. To date, tDCS effects on hand dexterity have not been explored in MS [38]. The main objective of this work is to evaluate the effects in question. Stimulating the motor cortex, or removing the cerebellar inhibition over it, can be beneficial in improving dexterity in MS patients. Therefore, in this work, we thought of activating (anodal tDCS) the primary motor cortex (M1) contralateral to the most affected hand or inhibiting (cathodal tDCS) the cerebellar cortex (i.e., Purkinje cells) aiming to facilitate motor output.

## 2. Materials and Methods

This is a randomized, double-blind, crossover, and sham-controlled study. A crossover design has been chosen, so that each participant can act as his or her own control in an attempt to limit the inter-subject variability. In addition, such a design requires a smaller sample size compared to a parallel group design for the same statistical power [39]. However, one should acknowledge the limitations of this within-subject design, mainly, the time burden imposed on patients (longer participation time compared to the parallel-group design), and the possibility of a carry-over effect (e.g., potential neuroplastic effects induced by the preceding tDCS effects) or an order effect. The former effect cannot be formally ruled out, but was taken into consideration by including a washout period of 3 weeks between tDCS blocks, as done previously [40]. The latter effect could be controlled by counterbalancing the tDCS order among patients and could be statistically tested by adding the order as a covariate in the analysis of covariance (ANCOVA).

The study was approved by the institutional review board of the Lebanese American University, Lebanon (IRB registration #IRB00006954). All patients will voluntarily give their written informed consent prior to inclusion. The study will take place in conformity with the Declaration of Helsinki and its amendments.

### 2.1. Study Participants

Patients presenting for consultation or hospitalization to the Neurology Department will be screened for eligibility. Patients (men and women) will be included if they fulfill the following criteria: (i) age between 18 and 70 years, (ii) presence of unilateral or bilateral upper extremity clumsiness as assessed by Chedoke Arm and Hand Activity Inventory version 13 (CAHAI-13) [41], (iii) definite MS diagnosis (relapsing-remitting, primary progressive, or secondary progressive) according to the 2017 McDonald criteria [42], and (iv) stable pharmacological and physical treatment for at least one month. Patients will be excluded if they have (i) had a relapse within the previous two months, (ii) severe upper limb weakness according to the Medical Research Council (MRC) grading system (MRC < 3 of the arm, forearm, or hand) [43], (iii) severe upper limbs spasticity as per the Modified Ashworth scale (MAS > 2) [44], (iv) severe dysdiadochokinesia (> 2) or dysmetria (>2) according to the ataxia scale [45], (v) severe sensory impairment as per the Semmes–Weinstein monofilament test (absence of sensation using monofilament E) [46], (vi) severe physical disability as per the Expanded Disability Status Scale (EDSS) (≥6.5) [47], (vii) apraxia as per the Apraxia Screen of TULIA (AST < 9) [48], (vii) depression as per the Beck Depression Inventory (BDI > 19) [49], or (viii) other neurologic and psychiatric diseases.

### 2.2. tDCS

A battery-driven stimulator (Sooma Oy, Helsinki, Finland) will deliver the current at an intensity of 2 mA through sponge electrodes soaked in a saline solution and having a surface area of 35 cm^2^ (Figure 1). For the real tDCS treatment, the current will be ramped up for 15 s until reaching 2 mA which will be maintained for 20 min; then it will be ramped down for 15 s at the end of stimulation. The current intensity, stimulation duration, and number of sessions were adopted from previous studies done on MS and other clinical populations [50,51]. For the sham condition, the current will be ramped up for 15 s, then progressively phased off, providing effective blinding [52,53]. The anode and the cathode will be placed according to the following design: for anodal motor tDCS (real/sham), the anode will be centered over M1 (at C3/C4, according to the international 10-20 EEG system) contralaterally to the most affected side with its reference electrode (cathode) placed over the contralateral forehead (AF8, 10-20 EEG system) (Figure 1). For cathodal cerebellar tDCS (real/sham), the cathode will be centered on the median line 2 cm below the inion with its lateral borders about 1 cm medially to the mastoid apophysis; its reference electrode (anode) will be placed over the right shoulder based on previous cerebellar tDCS studies (Figure 1) [54,55,56,57,58]. Preliminary modeling studies demonstrated that in this setup, the electric field distribution generated by cerebellar tDCS symmetrically involved the cerebellum, where the electric field distribution attained its peak.

### 2.3. Sample Size, Randomization and Blinding Effectiveness

In the absence of published data on this topic, the statistical outcomes of this study can serve in understanding and guiding the therapies of altered dexterity in MS patients. Previous tDCS studies addressing dexterity in stroke patients adopted sample sizes between 10 and 19 and yielded statistical significance [59,60].

In the absence of sham-controlled studies on this matter, sample size calculation was performed using the G*Power Software (version 3.1.9.6 [61]). A 2 × 3 within-subjects repeated measures analysis of variance was considered, with the factor time (before and after each stimulation condition) and the factor stimulation condition (active cathodal cerebellar, active anodal motor vs. sham). Considering the predicted medium effect size (f = 0.25) and adopting a two-tailed significant difference of α = 0.05 and an estimated power of 80%, the sample size estimate is 36. Taking into consideration a dropout rate of up to 25%, a sample of 45 patients will be sufficient to observe significant effects. *N* = 48 was adopted to be able to counterbalance the order of conditions as will be explained below.

Randomization will be performed by a researcher who will not be in contact with patients. In the first step, six different sets of blocks will be assigned, and each contains four patients: (active cathodal cerebellar, sham, active anodal motor), set B (active cathodal cerebellar, active anodal motor, sham), set C (sham, active cathodal cerebellar, active anodal motor), set D (sham, active anodal motor, active cathodal cerebellar), set E (active anodal motor, sham, active cathodal cerebellar), and set F (active anodal motor, active cathodal cerebellar, sham). In the second step, each set will be split into two subsets according to the sham setup, so that two patients per set will receive sham over the motor cortex (setup similar to active condition), and the other ones will receive sham over the cerebellum (setup similar to active condition). The flow chart of the protocol is displayed in Figure 2. The evaluators will assess the patients before and after tDCS blocks and will be blind to the stimulation conditions. Patients will be blind to the stimulation condition.

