### 2.5. Experimental Protocol

The first visit is an inclusion visit, where the examining physician will perform the neurologic exam, and verify the inclusion and exclusion criteria. Patients will obtain information regarding the protocol, consent form, and the other questionnaires to be filled. They will be called in the following days to check if he/she agrees to participate in the study and therefore to plan the stimulation sessions. In case of acceptance, an appointment will be scheduled in order to sign the consent form and deliver a booklet containing the VAS for pain to be filled for one week prior to the stimulation week and during the week of stimulation. If present, medications and physical therapy will be kept the same as the previous month. Patients will be asked to restrict stimulant consumptions (e.g., caffeine, nicotine) at least three hours prior to their appointments.

Each patient will be randomly assigned to receive 3 blocks separated by a washout interval of three weeks (anodal tDCS over M1 contralateral to the most affected hand, cathodal tDCS over the cerebellum, and sham over either cortical site). Each block will consist of five 20-min stimulation sessions, applied on day 1 to day 5 (D1 to D5). On D1, dexterity will be quantified based on the time required to perform the 9-HPT. Each patient will be evaluated for fatigue (MFIS), anxiety and depression (HADS), spasticity (MAS), motor power (MRC), and cerebellar function (ataxia scale). Afterwards, tDCS will be performed in a quiet and well-illuminated room with the patient sitting in an armchair without any concurrent cognitive or motor task. The stimulation session will be repeated from D1 to D5. At the end of D5 session, each patient will undergo the same evaluation as done on D1 (9-HPT, MFIS, HADS, MAS, MRC, ataxia scale), as well as the CRQ, CGI, and will be delivered a VAS booklet (pain) to be filled for one week following D5 and for one week prior to the next tDCS block. 

Each patient will be included in the study for 3 months. 2 patients per week will undergo the stimulation block. The study will take place for a total duration of 12 months, and the final data analysis will be performed in less than a year. The schematic diagram of the protocol is illustrated in Figure 3. 

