### 2.9. Statistical Analysis

The statistical analysis will be performed using the SPSS software (IBM Corp. Released 2016. IBM SPSS Statistics for Windows, Version 24.0. Armonk, NY: IBM Corp). The primary and secondary outcomes will be analyzed using the same statistical approach. For all variables, the normality of data distribution will be tested using the Kolmogorov–Smirnov test. The homogeneity of variance will be tested using the Levene’s test. Depending on the data distribution, the scores obtained before and after all tDCS conditions will be compared using the repeated measures analysis of variance (ANOVA) or the Friedman test under six conditions: 2 times (before and after tDCS) × 3 stimulation conditions (anodal motor tDCS, cathodal cerebellar tDCS, and sham). When appropriate, the post hoc Dunn’s test will be applied. Two-tailed p-values less than 0.05 will be considered significant. Data will be presented as the mean ± the standard deviation or the median (1st and 3rd quartiles).

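### Sham site is randomised, but the stated analysis pools the two shams and has no sham-site term, so it cannot show whether active-versus-sham contrasts depend on the sham montage

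*Protocol article*

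**What the plan says.** Section 2.3 of the protocol article allocates patients in two steps. The first assigns one of the six possible orders of motor active, cerebellar active and sham. In the second, "each set will be split into two subsets according to the sham setup": two of the four patients in a set have sham with the motor montage and two with the cerebellar montage.

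Section 2.5 confirms that each patient has three blocks, with one sham block at one site: anodal stimulation of the motor area, "cathodal tDCS over the cerebellum, and sham over either cortical site".

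Section 2.2 shows that the montages are plainly different for the patient. The motor set-up has its reference electrode on the forehead. The cerebellar set-up has an electrode below the inion and a reference on the right shoulder.

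The analysis in section 2.9 crosses two times with "3 stimulation conditions (anodal motor tDCS, cathodal cerebellar tDCS, and sham", by repeated measures ANOVA or, depending on the distribution, a Friedman test. The sample size in section 2.3 uses the same structure: "A 2 × 3 within-subjects repeated measures analysis of variance was considered". The only further covariate mentioned is treatment order, in the opening of section 2. Sham site appears in neither the model nor the sample size. Section 2.4.2 collects an active/sham guess at the end of each block.

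**The concern.** A sham controls for expectation, sensation and procedure when it resembles the active condition it is compared with. Section 2.3 recognises this by specifying that each sham uses the same set-up as its active counterpart. Yet in half the patients each active condition is compared with a sham that looks and feels different, and the analysis does not separate the two halves. Any difference between the shams in expectation or sensation then enters both treatment contrasts, raising one and lowering the other. The primary outcome is a timed performance task, on which effort and expectation could plausibly act.

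The article does not leave the model open. It fixes the factors, and the fixed model omits one that the trial itself randomises. A significant pooled contrast could therefore not be checked, under the stated plan, for whether it holds against the matched sham.

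**Working it through.** **Inputs.** From section 2.3: six orders; sham site 1:1 within each order; adopted N = 48; "Considering the predicted medium effect size (f = 0.25"); "two-tailed significant difference of α = 0.05 and an estimated power of 80"%; "the sample size estimate is 36" before dropout. The correlation between repeated measures is not given. Section 2.3 writes four patients per set, which makes 6 × 4 = 24; N = 48 needs eight per set. The fractions below hold either way.

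**Step 1. The plan's own figure.** For a within-subject effect, take λ = N·m·f²/(1 − ρ) with degrees of freedom m − 1 and (N − g)(m − 1), where m is the number of measurements and g the number of groups. N = 36 results, for example, with g = 3, m = 2, ρ = 0.5 (λ = 36 × 2 × 0.0625/0.5 = 9.0; power 0.829) or with g = 1, m = 6, ρ = 0 (λ = 36 × 6 × 0.0625 = 13.5; power 0.809). So 36 is reproducible, though only under settings that the article does not state. None of these settings involves sham site, and the point does not depend on which was used. With 25% dropout, 48 × 0.75 = 36 completers.

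**Step 2. How often is the sham matched?** Write M and C for the montage in each block.

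| Order (a = active, S = sham) | Motor sham | Block with once-only montage | Cerebellar sham | Block with once-only montage |
|---|---|---|---|---|
| Ma, Ca, S | M C M | 2 | M C C | 1 |
| Ma, S, Ca | M M C | 3 | M C C | 1 |
| Ca, Ma, S | C M M | 1 | C M C | 2 |
| Ca, S, Ma | C M M | 1 | C C M | 3 |
| S, Ma, Ca | M M C | 3 | C M C | 2 |
| S, Ca, Ma | M C M | 2 | C C M | 3 |

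Motor active has a motor sham in 6 of 12 combinations, and cerebellar active has a cerebellar sham in the other 6. That is 50% each: 24 of 48 patients, or 18 of 36 completers if dropout is balanced (12 of 24 as the sets are written).

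In all 12 combinations the once-only montage is active. It falls in block 3 in 4 of 12, one third of patients (48 × 4/12 = 16).

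**Step 3. What pooling does.** Let A_M, A_C, S_M and S_C be the mean within-block changes and d = S_M − S_C. With a 1:1 split the pooled sham mean is (S_M + S_C)/2. Then

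- motor: A_M − (S_M + S_C)/2 = (A_M − S_M) + d/2
- cerebellar: A_C − (S_M + S_C)/2 = (A_C − S_C) − d/2

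The shift is zero if d = 0. The article neither gives d nor plans to look at it. For illustration, assume d between 0.2 and 0.5 SD of the paired difference. A contrast whose matched version is truly null then has a standardised pooled difference of 0.1 to 0.25. A two-sided 0.05 paired t-test rejects it about 9% to 31% of the time with 36 pairs, and about 10% to 40% with 48.

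**Step 4. Precision of the matched contrasts.** Assume a standardised paired difference dz = 0.5, which follows from f = 0.25 for two conditions only if the correlation is 0.5: 2f/√(2(1 − ρ)) = 0.5/1. Paired t-test power, two-sided 0.05:

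| Pairs | dz = 0.3 | dz = 0.5 | dz = 0.7 |
|---|---|---|---|
| 18 (matched completers) | 0.23 | 0.52 | 0.80 |
| 24 | 0.29 | 0.65 | 0.91 |
| 36 (all completers, pooled) | 0.42 | 0.83 | 0.98 |

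**The case against.** The defence has real substance. The 1:1 split within each order stops either active condition from monopolising the matched sham. Pooling is unbiased if the two shams act alike, and the article offers no evidence that they differ. With complete data, the site-averaged contrast has the same point estimate as the pooled one, so the primary result would hardly move. A sensitivity analysis is also the kind of detail that an unseen analysis plan may contain. And a check for a sham-site difference would be weak: comparing 18 with 18 completers has power of only about 0.31 for a difference of 0.5 SD.

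All of this limits the point, but does not remove it. The article does state the factors of the model, and the randomised one is absent.

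Three stronger readings are tempting and not supported.

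- A reader might infer that the treatment contrasts are biased. That requires d to differ from zero, which is unknown.
- A reader might infer that one third of patients will recognise block 3 as active before it starts. Knowing that one block is sham is not enough: after motor, motor, cerebellar, a patient could still suppose that both motor blocks were active. The patient must also know or infer that the two active blocks use different sites. Section 2.5 says only that patients receive information about the protocol, and the consent material is not available.
- A reader might infer that blinding is weaker in the unmatched half. This is not shown; patients in the matched half feel active and sham at the same site and can compare them directly.

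**Conclusion.** The point holds as a gap in the stated analysis, not as a demonstrated bias. In half the patients each active condition is compared with a sham at the other site. The pooled contrast can differ from the matched one by half of any sham-site difference, with opposite sign for the two active conditions, and the stated model cannot reveal it.

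The 50% share follows from the allocation rule alone. The count of 24 of 48 assumes eight patients per set. The rejection rates rest on assumed values of d, and the power figures on an assumed dz.

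That the once-only montage is always active is a certain feature of this design. Its effect on blinding is conditional on what patients know, and no analysis can undo it; the guesses can only help to describe it. The change is worth making because the factor is already randomised and the guesses are already collected.

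**What to change.** Change the analysis wording in section 2.9:

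- Analyse within-block change with sham site as a between-patient factor, and include sham site × condition. If time stays in the model, the term needed is sham site × condition × time; sham site × condition alone would not address the effect of interest.
- Use a model that can carry this factor. The Friedman test cannot, so the non-normal case needs another fallback.
- Keep the contrast averaged over sham site as primary.
- Pre-specify the montage-matched contrasts (motor active against motor sham, cerebellar active against cerebellar sham) as a supportive sensitivity analysis.
- Tabulate the end-of-block active/sham guesses by sham site and by matched or unmatched montage.
- State the number of patients per set so that it agrees with N = 48.

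The cost is wording only: no extra patients, visits or measurements. The downside is imprecision. With about 18 matched pairs the sensitivity contrasts have roughly 0.52 power under dz = 0.5, so a non-significant matched contrast or interaction must not be read as evidence that the shams are equivalent. Report estimates with confidence intervals.
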